### Adaptations at interim analysis (end of stage 1)

Interim analysis at the end of stage 1 will assess whether any of the five intervention arms should be dropped as recommended by an independent Data Monitoring and Safety Board (DSMB) based on a three-part criteria. First, an arm whose statistical comparison to the SOC arm yields a *p* value > 0.2 will be considered for dropping for futility. Second, any intervention arm with a *high* incidence of SAEs, i.e. grades 3, 4 or 5 (Table 3) compared to SOC will be considered for dropping. It is at the discretion of the DSMB to decide, based on absolute number of SAEs in each intervention trial arm, whether they are high or not. Such an observation and recommendation will then be shared with the investigators who will make the final decision. Thirdly, an arm may be maintained after taking into account the costs associated with providing the service in light of the *p* value from statistical analysis. For this cost analysis, we will provide the DSMB estimates of the incremental cost per male partner tested, and incremental cost per HIV-positive male identified through the intervention arms in comparison to the SOC arm. The investigators will access the first-stage data only after the last follow-up visit for participants has occurred in order to perform interim analysis. The CRT extension to the Consolidated Standards of Reporting Trials (CONSORT) [37] will be followed when reporting the data.

**Table 3 Tab3:** Adverse event grading

Grade 1 (Mild)	Grade 2 (Moderate)	Grade 3 (Severe) (within 30 days)	Grade 4 (Potentially life-threatening) (within 30 days)
1. Verbal, emotional or psychological intimate-partner violence (IPV) 2. Denying access to household resources 3. Being ignored 4. Being controlled (e.g. not allowed to leave house)	1. Coercion to self-test. 2. Coercion to disclose a self-test result 3. IPV that includes pushing, or slapping with an open hand that does not result in pain, or visible marks >24 h 4. Severe or prolonged psychological or emotional IPV leading to disruption of daily activities 5. Psychologically coercive sex	1. IPV that leads to pain, bruising or marks >24 hr 2. Threat of life-threatening violence (e.g. statement of intent to kill, mock strangulation, threatened with a knife or gun) 3. Physically coercive sex 4. Reports fearing for her life 5. Marriage break-up	1. IPV leading to hospitalisation or death 2. Suicide or attempted suicide 3. Attack using potentially lethal force (e.g. knife, gun, hammer, kicks to the head)

Grade 1 indicates a mild event

Grade 2 indicates a moderate event

Grade 3 indicates a severe event

Grade 4 indicates a potentially life-threatening event

Grade 5 indicates death: not indicated on the table

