### Primary and secondary outcomes

The primary outcome is the proportion of male partners of ANC attendees who test for HIV and link into HIV care or prevention within 28 days of enrolling the woman (Fig. 3). Thus, the primary outcome is defined as presentation of the male partner at the MFC with a used self-test kit (if in the intervention arm) or undergoing spot HIV testing with a study HIV counsellor within 28 days AND being referred for HIV care if HIV positive or VMMC if HIV negative and uncircumcised. There are four secondary outcomes: the proportion of male partners who test for HIV within 28 days (as reported by the woman); the proportion of women who accept to participate in their allocated trial arm; risk of serious adverse events (SAEs) in men and women in the study; and the total cost of implementing each trial arm. All outcomes will be analysed at cluster level (see the ‘Statistical analysis’ section).

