### Outcome measurement

All male partners who present at the MFC in the SOC arm will be offered a single finger-prick HIV test with Determine 1/2™ as per Malawi national testing algorithm. An HTS counsellor will re-read a used self-test kit if the participant returns one as evidence of self-testing in the intervention arms. Participants who return with unused self-test kits or without self-test kits will be requested to self-test in the presence of the counsellor. All HIV results will be recorded on a data form followed by confirmation of HIV-positive results in parallel using Determine 1/2™ and Uni-Gold, with facilitated linkage to HIV care. All men who test HIV negative and report to be uncircumcised will be offered VMMC to be conducted by Population Services Internal (PSI). Thus, measurement of primary outcome includes evidence of an HIV test, confirmatory testing, and referral to HIV care or VMMC as appropriate within 28 days of the woman being recruited.

The secondary outcome of HIV testing among male partners will also be measured though proxy reporting by the woman using audio computer-assisted self-interview (ACASI) during her next ANC visit 4 weeks later. Participation in the allocated trial arm will be measured by computing the proportion of women who accept to participate after receiving trial-arm-specific information using the denominator of the total number of women who are eligible. All women will be asked to report any adverse events through ACASI at their next ANC visit while men who present to the MFC will be asked to report any adverse events. A costing tool validated in urban Blantyre [31] will be used to capture the costs associated with providing the service in each trial arm. The cost and outcome data will be used to estimate the cost per male partner tested for HIV, and cost per HIV-positive male identified through all SOC and intervention arms.

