The trial results will also have important policy implications on how to implement HIVST targeting male partners of pregnant women who are accessing ANC for the first time while paying particular attention to safety concerns. In a recent cohort study where HIV-negative pregnant women collected three oral self-test kits in Kenya 51% reported that their male partners had self-tested with none of the women reporting any SAEs [40]. Unlike in the Kenya study, where only HIV-negative pregnant women were eligible, this trial will recruit pregnant women, regardless of HIV status, who are attending their first ANC. The group of women recruited here receive the offer of an HIV test routinely making this trial design readily scalable. Measuring actual HIV testing is extremely difficult with HIVST as by definition disclosure depends on the individual. Our HIV testing outcome will be measured objectively through observed returned used/unused self-test kits by the man and also proxy reporting by the woman which minimises information bias.

A major anticipated constraint is potential for SAEs resulting mainly from intimate partner violence (IPV) to women, although evidence from studies using other populations and other HTS models suggests that this approach is unlikely to increase this problem [6]. A recent large HIV self-testing study in Malawi found no increase in IPV, despite an active community liaison system among 27,000 self-testing participants [20]. We will carefully monitor IPV, and have deliberately listed this as a secondary (safety) outcome. Although it will not be possible for participants and recruiting staff to predict the next-day recruiting arm, the knowledge of FI arms may result in altered decision-making about health care seeking. For example, a woman may choose to postpone her ANC attendance in the hope of being recruited in a FI arm, or indeed want to switch between arms.

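### The interim safety criterion is worded both as incidence against SOC and as an absolute SAE count, and men are asked about events only if they attend the clinic, so the male-reported part is not comparable between arms

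*Protocol article*

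**What the plan says.** The Protocol article, under 'Adaptations at interim analysis (end of stage 1)', makes safety the second of three criteria for dropping an arm. The criterion is first stated as a comparison of incidence with SOC: "incidence of SAEs, i.e. grades 3, 4 or 5 (Table 3) compared to SOC will be considered for dropping". The next sentence leaves it to the DSMB to decide, "based on absolute number of SAEs in each intervention trial arm, whether they are high or not". That sentence gives no denominator and does not mention the SOC arm. No numerical threshold is set, and the investigators take the final decision on the DSMB's recommendation.

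'Primary and secondary outcomes' defines the safety outcome as "risk of serious adverse events (SAEs) in men and women in the study", so events in both sexes count. 'Outcome measurement' collects them differently. For women: "All women will be asked to report any adverse events through ACASI at their next ANC visit". For men: "while men who present to the MFC will be asked to report any adverse events". Attendance at that clinic also underlies the efficacy measure: "the primary outcome is defined as presentation of the male partner at the MFC", together with evidence of testing and referral within 28 days.

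The Discussion expects most harm to fall on women: "A major anticipated constraint is potential for SAEs resulting mainly from intimate partner violence (IPV) to women".

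**The concern.** There are two linked problems.

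1. **Contradiction.** An incidence compared with SOC has a denominator and a comparator. An absolute number in each intervention arm has no denominator, and the sentence names no comparator. A DSMB reading this section cannot tell which quantity it is meant to judge.

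2. **Ascertainment that depends on the arm.** The number of men who are asked about events is the number who attend the clinic. Raising that number is the purpose of the interventions, and three arms offer money or a lottery entry for doing so. At the same true risk per man, an arm that raises attendance is expected to yield more male-reported SAEs than SOC. The male part of the count thus mixes safety with efficacy.

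At stake is a criterion that can contribute to ending recruitment to an arm. The same mechanism works in the other direction: an event known only to the man is less likely to be recorded in an arm where few men attend.

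**Working it through.** The article gives no figure for the SAE criterion, so there is none to reproduce. The check uses its sample-size inputs.

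**Inputs from the article**
- Cluster size ('Sample size considerations'): 40 women × 0.9 eligible × 0.6 consenting = 21.6, stated as at least 21. This reproduces.
- Six clinic days per arm in stage 1: n = 6 × 21 = 126 couples per arm.
- Primary outcome: 25% in SOC and 40% at the target effect ('Sample size considerations'); 29% to 40% in the simulated intervention arms (Table 1).

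**Assumptions, not in the article**
- The share of men attending equals the primary-outcome rate p.
- r_w and r_m, the reported SAE risks in women and men: 1% to 5% each, the same in all arms.
- a_w, the share of women interviewed: 70% to 100%, the same in all arms.

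**Step 1: men asked per arm = n × p**

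| p | Men asked | Ratio to SOC |
|---|---|---|
| 25% (SOC) | 126 × 0.25 = 31.5 | 1.00 |
| 29% | 126 × 0.29 = 36.5 | 0.29/0.25 = 1.16 |
| 40% | 126 × 0.40 = 50.4 | 0.40/0.25 = 1.60 |

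At equal r_m, the ratio of expected male-reported SAEs is the ratio in the last column.

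**Step 2: both sexes combined**

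Expected count per arm = n × (a_w × r_w + p × r_m). At 40% v 25%:
- Smallest inflation (r_w = 5%, r_m = 1%, a_w = 1): (0.05 + 0.0040)/(0.05 + 0.0025) = 0.0540/0.0525 = 1.03.
- Largest (r_w = 1%, r_m = 5%, a_w = 0.7): (0.007 + 0.0200)/(0.007 + 0.0125) = 0.0270/0.0195 = 1.385, the upper end of the 1.03 to 1.39 range.
- Equal risk in both sexes, all women interviewed: (1 + 0.40)/(1 + 0.25) = 1.12.
- Excess events per arm: 126 × (0.40 − 0.25) × r_m = 18.9 × r_m, which is 0.2 to 0.9.
- If every male-reported event duplicates one reported by the woman and is counted once, the male term drops out and the ratio is 1.00.

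**Step 3: chance variation**

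With independent Poisson counts, equal risk in both sexes and all women interviewed, at 40% v 25%:

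| Risk | More SAEs than SOC | Fewer SAEs than SOC |
|---|---|---|
| 1% | 43% | 35% |
| 3% | 51% | 37% |
| 5% | 54% | 36% |

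**Step 4: which denominator removes the effect**
- Per enrolled woman: n is the same in both arms, so the male ratio stays 0.40/0.25 = 1.60. 'Statistical analysis' uses eligible women as its denominator, so a rate on that basis would not help.
- Per person asked, by sex: for men, (50.4 × r_m/50.4)/(31.5 × r_m/31.5) = 1.00, and likewise for women per woman interviewed.

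**The case against.** The strongest reply is that most of the safety information is not affected. All women are asked in the same way in every arm, whether or not the partner attends, and the Discussion expects SAEs mainly in women. This stands, and it limits the point. The 1.60 applies to male reports alone and must not be read as the inflation of an arm's total. It also belongs to the largest simulated effect. Four of the five simulated arms lie at 29% to 32%, giving male-only ratios of 0.29/0.25 = 1.16 to 0.32/0.25 = 1.28.

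Second, 25% and 40% are rates of the primary outcome, not of attendance. A man who attends late, or who does not complete testing and referral, can still be asked. A reader might infer that 75% of SOC men are never asked; the article does not give that figure.

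Third, with 1:1 allocation and six days per arm, planned arm sizes are equal, so counts and rates per enrolled participant would rank arms much alike. That makes the conflict between the two sentences milder in practice. It does not help with the male reports, because neither quantity allows for the number of men asked.

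Fourth, the layout of DSMB tables commonly sits in a charter or analysis plan, and its absence here is no fault. But the article does state the quantity to be judged, in two incompatible ways, and it states the rule for asking men.

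A reader might go further and infer that effective arms will show more SAEs, or that the criterion would remove the best arm. The article does not support either. The excess holds in expectation only, and Step 3 shows an effective arm often has fewer events than SOC. There is no automatic threshold, and an expected excess below one event per arm would be weighed by a board using its discretion.

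**Conclusion.** The point holds in a limited form and is minor. The two sentences of the safety criterion contradict each other. Separately, male-reported SAEs are collected through a channel whose size depends on the arm, so neither raw counts nor rates per enrolled woman are comparable between arms for the male part.

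At equal true risk, and if attendance equals the primary-outcome rate, the male-only ratio is 1.16 at 29% and 1.60 at 40%. For both sexes combined at 40% v 25% it is about 1.03 to 1.39, or 0.2 to 0.9 extra events per arm, under the assumed risks and interview coverage. It is 1.00 if male reports only duplicate women's and are counted once; the article does not say how such reports are handled.

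The direction of the effect follows from the text; its size rests on these assumptions. DSMB discretion limits the consequence but does not make the male counts comparable. Nor does the point justify treating male reports as merely supportive: events in men and women are both part of the stated safety outcome.

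**What to change.** 1. Reconcile the two sentences under 'Adaptations at interim analysis (end of stage 1)' so that they name one quantity and one comparator.
2. Give the DSMB, for every arm including SOC, the number of SAEs, the number of people asked and the rate, separately for women (per woman interviewed) and men (per man attending the clinic).
3. Identify events reported by both partners, so that the DSMB can see the overlap.
4. Add a note that attending men are a selected group whose number depends on the arm. A rate per attending man removes the effect of numbers asked, but not any difference between men who attend and men who do not.

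The judgement of what is high, and the weight given to male reports, stay with the DSMB. The cost is a revised DSMB table and a few sentences. The counts of women interviewed and men attending come from the planned visits, so no new data collection is needed.

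### The 30-day limit on severe events has no start date and does not match how events are collected, and the number of men asked about harm follows the primary outcome

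*Protocol article*

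**What the plan says.** All references are to the protocol article.

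- **Window.** Table 3 (Adaptations at interim analysis) heads two columns "Grade 3 (Severe) (within 30 days" and "Grade 4 (Potentially life-threatening) (within 30 days". It gives no start date. Grades 1 and 2 carry no time limit.
- **Collection.** Outcome measurement states: "All women will be asked to report any adverse events through ACASI at their next ANC visit while men who present to the MFC". Those men are questioned likewise when they attend. The same section places the woman's computer-assisted interview "during her next ANC visit 4 weeks later".
- **Linkage period.** Under Primary and secondary outcomes, a man counts if he tests and links "within 28 days of enrolling the woman". Under Intervention arms, every cash incentive depends on his linking to the clinic.
- **Use.** SAE risk in men and women is a secondary outcome. At interim, a high incidence of grades 3 to 5 relative to standard of care is the second of three criteria for dropping an arm. The DSMB judges it from the absolute number of SAEs in each intervention arm.
- **Grading of death.** Grade 4 lists "IPV leading to hospitalisation or death" and, as a separate item, suicide. The footnote says "Grade 5 indicates death: not indicated on the table".

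**The concern.** A count that can remove an arm should be taken over the same observation time, and from people asked with the same probability, in every arm. Two features work against this.

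First, the 30-day limit, the 4-week interview and the 28-day linkage period are not tied to one clock. A reader cannot tell which severe events count, or whether the interview can see all of them.

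Second, men are questioned only on attending the clinic, and attendance is what the interventions are meant to raise. An arm that works therefore has more men asked about harm than standard of care, whatever the true risk. If men's and women's reports go into one absolute number, part of any excess in a successful arm may come only from asking more men.

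**Working it through.** **1. What the 30 days could mean.** The article does not choose between these readings.

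- *From enrolment.* An on-time interview at day 28 misses 30 - 28 = 2 days (2/30 = 7%), the same in every arm. If a woman comes late and reports a severe event on day 35, it has no grade 3 or 4 to fall into.
- *From the test or payment on day t.* The woman's day-28 interview covers 28 - t days and leaves 30 - (28 - t) = 2 + t uncovered:

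| t (day) | Days covered | Days uncovered | Share of 30 uncovered |
|---|---|---|---|
| 0 | 28 | 2 | 7% |
| 7 | 21 | 9 | 30% |
| 14 | 14 | 16 | 53% |
| 21 | 7 | 23 | 77% |
| 28 | 0 | 30 | 100% |

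- *As recall before the interview.* An on-time interview fits, since 28 is below 30. A late one drops the earliest days after enrolment.

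The values of t are an assumed range. The article gives no distribution of test or linkage dates, overall or by arm.

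**2. What a man's own report covers.** He is asked when he presents, and payment depends on that visit. Time observed after payment is therefore 0 days in the three incentive arms. Time observed after the test result is 0 days under standard of care and for men tested on the spot. For a man who returns a used kit, it is the interval from home test to visit.

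**3. How many men are asked.** Inputs are from Sample size considerations: 40 women per day, 90% eligible, 60% consenting, 25% linkage under standard of care, a 15-point target difference, and six days per arm.

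- Cluster size: 40 x 0.9 x 0.6 = 21.6, which agrees with the article's figure of at least 21.
- Women per arm in stage 1: 6 x 21 = 126.
- Men asked under standard of care: 126 x 0.25 = 31.5, about 32. Not asked: 75%.
- Men asked in an arm at 40%: 126 x 0.40 = 50.4, about 50. Not asked: 60%.
- Men asked at 29%, the lowest intervention rate in the article's simulation: 126 x 0.29 = 36.5, about 37.
- Ratio at the target effect: 0.40/0.25 = 1.6, the article's own 1.6-fold increase.

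This takes the men who meet the primary outcome as an approximation to the men who attend. If each man asked reported an SAE with the same probability r in both arms, the expected counts from men would be 31.5r and 50.4r. The second is 1.6 times the first with no difference in risk.

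**4. Grading of death.** The interim criterion pools grades 3, 4 and 5, so a death counts as an SAE under either grade. The conflict matters only through the time limit: grade 4 carries 30 days, while none is stated for grade 5. A violent death or a suicide outside 30 days would count under the footnote but might not under the grade 4 column.

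**The case against.** The strongest reply has four parts.

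- **Women are followed alike.** Every arm has the same interview at the same nominal time, and the article dates its primary outcome from enrolment. On that clock the gap is 2 days against a nominal 4-week visit. This stands.
- **Unequal timing across arms is not shown.** A reader might infer that harm is cut off by different amounts across arms because incentives and reminders shift both the man's visit and the woman's return. The documents do not support this. The incentives, lottery and phone call are directed at the man, and nothing ties them to the woman's next antenatal visit. Testing at home before the visit makes a timing difference plausible, but neither its size nor its direction can be derived.
- **Harm after payment is not shown to be mostly unobserved.** That inference needs an assumed distribution of linkage dates. Even with linkage spread evenly over 28 days, which the article does not support, the woman's interview would see 14 days on average after the man's visit. Only three of the five intervention arms pay, and most of the violence items in Table 3 concern the woman, who is interviewed separately.
- **Other reporting routes may exist.** The assessment schedule (Fig. 3), the additional file and the full protocol are not shown. Death and suicide cannot be self-reported, so some other route is likely. This limits any claim that nothing else is collected.

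None of this supplies the missing start date, reconciles the grade 4 and grade 5 wording, or changes the fact that the number of men asked follows the primary outcome.

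**Conclusion.** The point holds in a limited form. The 30-day limit has no start date and is not reconciled with the 4-week interview or the 28-day linkage period. For women the consequence is 2 days, equal across arms, if the clock is enrolment. It is between 2 and 30 days if the clock is a test or payment between day 0 and day 28. Men's reports cover no time after the visit.

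The firmest consequence for the decision rule is the number of men questioned: about 32 of 126 at 25% linkage against about 50 of 126 at 40%. It bears on the DSMB criterion if men's and women's events enter one absolute count per arm, which the article's wording allows and does not rule out. The figures assume the design linkage rates and 21 women per day. The 1.6 ratio does not depend on cluster size.

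The conflict over death and suicide is real, but it alters the pooled grade 3 to 5 count only through the 30-day limit.

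**What to change.** - State the start of the 30 days, and reconcile it with the 4-week interview and the 28-day linkage period.
- Add the date of each event to the woman's computer-assisted interview.
- Give the DSMB women's SAEs in one common window from enrolment, the same in all arms, and list later-reported events separately.
- Tabulate men's clinic reports apart from women's, with the number of men asked as denominator, and state that they cover only the time before the visit.
- Reconcile the grading of death and suicide between Table 3 and its footnote.

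The cost is one interview item, some wording and one more table, with no extra visit. Recall of dates will be imperfect. Trial status reports 32 of 36 stage 1 clusters already covered, so the new item would mainly serve stage 2, whereas separate tabulation of men needs no new data collection and could be used at the interim analysis. Harm after a late clinic visit stays unobserved by these two sources and should be stated as a limitation.
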